## 8.2 Baseline data:

|                                                                                                                                                                                                        |                                                         |
|--------------------------------------------------------------------------------------------------------------------------------------------------------------------------------------------------------|---------------------------------------------------------|
| Age of the patient                                                                                                                                                                                     | Continuous                                              |
| Use of contraception                                                                                                                                                                                   | Categorical                                             |
| Smoking                                                                                                                                                                                                | Dichotomous                                             |
| Previous surgery for ovarian cysts 
 
- Number of surgeries
 
- Laparoscopy
 
- Laparotomy
 
                                                | Dichotomous
Continuous
Dichotomous
Dichotomous |
| Indication for surgery: pain and/or infertility                                                                                                                                                        | Categorical                                             |
| Pain pattern (+NRS for each parameter): 
 
- Dysmenorrhea
 
- Chronic pelvic pain
 
- Dyspareunia
 
- Dyschezia
 
- Dysuria
 
 | Continuous                                              |
| Infertility 
 
- Duration
 
- Primary or secondary
 
                                                                                               | Continuous
Dichotomous                               |
| Gravida/ Para                                                                                                                                                                                          | Categorical                                             |
| BMI (kg/m  )                                                                                                                                                                               | Continuous                                              |
| Diameter of the cysts (in mm)                                                                                                                                                                          | Continuous                                              |
| Cyst wall surface                                                                                                                                                                                      | Continuous                                              |
| Uni or bilateral endometrioma                                                                                                                                                                          | Dichotomous                                             |
| Baseline AMH value                                                                                                                                                                                     | Continuous                                              |

### Surgical data:

|                                       |            |
|---------------------------------------|------------|
| Total operative time (min)            | Continuous |
| Operative time for endometrioma (min) | Continuous |

|                                                                                                                                                                                                                                                                                  |             |
|----------------------------------------------------------------------------------------------------------------------------------------------------------------------------------------------------------------------------------------------------------------------------------|-------------|
| Hemostatic method used to manage the bleeding on each ovary 
 
- Not required (no bleeding)
 
- Selective bipolar coagulation + hemostatic device used + power settings
 
- Suturing
 
- Hemostatic sealants
 
 | Categorical |
| rAFS points                                                                                                                                                                                                                                                                      | Continuous  |
| rAFS stage                                                                                                                                                                                                                                                                       | Ordinal     |
| EFI                                                                                                                                                                                                                                                                              | Ordinal     |
| Hospital stay (days)                                                                                                                                                                                                                                                             | Continuous  |
| Follow up postoperativeley (months)                                                                                                                                                                                                                                              | Continuous  |
| Complications: 
 
- Clavien-Dindo grade I
 
- Clavien-Dindo grade II
 
- Clavien-Dindo grade III
 
- Clavien-Dinco grade IV
 
                                                                                  | Ordinal     |

## Postoperative follow-up

|                                                                                                                                                                                                                                                |             |
|------------------------------------------------------------------------------------------------------------------------------------------------------------------------------------------------------------------------------------------------|-------------|
| Pain pattern (+NRS for each parameter): 
 
- Dysmenorrhea
 
- Chronic pelvic pain
 
- Dyspareunia
 
- Dyschezia
 
- Dysuria
 
                                         | Continuous  |
| Recurrence at ultrasound                                                                                                                                                                                                                       | Dichotomous |
| AMH value                                                                                                                                                                                                                                      | Continuous  |
| Child wish 
 
- Non-ART 
 
o Spontaneous
 
o IUI
 
 
 
- ART 
 
o IVF
 
o ICSI
 
 
 
 | Dichotomous |

Summary tables (descriptive statistics and/or frequency tables) will be provided for all variables (baseline, surgical and postoperative follow-up).

Continuous variables will be summarized with descriptive statistics (n, mean, standard deviation, range, median, p25 and p75).

Frequency counts and proportions of subjects within each category will be provided for the categorical data.

#### Procedure(s) to account for missing data:

Since patients will be randomized after baseline measurements, baseline measurements are available for all randomized patients. We will avoid missing data by using a e-CRF that can only be saved if all necessary data is correctly filled out. Further, in the statistical analysis a modeling approach (direct likelihood approach for the cLDA model on longitudinal data) will be used incorporating all available information, i.e. also subjects with one or more timepoints with a missing outcome are still included in the analysis.

### **8.3 Primary study parameter(s)**

Evaluation of serum AMH at 3 months follow up.

It concerns an intention to treat analysis. All participants will be included in the analysis in the groups to which they were originally assigned, regardless of what subsequently occurred.

To handle the presence of missing values (due to dropout or to pregnancy, in the latter case AMH values after pregnancy are put on missing), a constrained longitudinal data analysis (cLDA, cfr Liang and Zeger, 2010) will be used instead of an ANCOVA to evaluate the differences between the groups in the final analysis. In this approach both the baseline and post-baseline values are modeled as dependent variables, as opposed to a longitudinal ANCOVA model in which the baseline value is included as a covariate. Although the baseline measure is included in the response vector in cLDA, the true baseline means are constrained to be the same for different treatment groups due to randomization, and this analysis provides an adjustment for the observed baseline difference in estimating the treatment effects. Center will be added as a factor in the model. A (logarithmic) transformation of the AMH will be considered to obtain a more symmetric distribution of the model residuals. Using a direct likelihood approach for the cLDA model, a subject with a missing measurement at three months is not excluded from the analysis. As such, the analysis does not assume missing completely at random (MCAR), but is still valid under missing at random (MAR).

References: Liang, K. Y. and Zeger, S. (2000). Longitudinal data analysis of continuous and discrete responses for pre-post designs. *Sankhya: The Indian Journal of Statistics, Series B* 62, 134–148.

#### **8.4 Secondary study parameter(s)**

##### AMH at other timepoint

The cLDA model used for the AMH at 3 months will be extended with the other timepoints for the evaluation of the AMH at 6 and 12 months.

##### AMH /cyst surface at 3, 6 and 12 months follow up

The ratio of the AMH and the cyst surface will be analyzed using the same methodology as used for the AMH.

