### **4.2 Inclusion criteria**

In order to be eligible to participate in this study, a subject must meet all of the following criteria:

- Age: 18 – 40 years (both inclusive)
- Unilateral endometriotic cysts with a mean diameter of  $\geq 2.5$ cm and  $\leq 8$  cm, measured in 3 dimensions.
- Presence of a contralateral endometrioma of  $\leq 2$ cm is allowed
- Complaining of infertility and/or pain
- BMI  $\leq 35$
- Use of contraception OCP? (combined or Progesteron only) for at least 4 weeks before surgery

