#### 6.1.2 Secondary study parameters/endpoints

- AMH difference/cyst surface between baseline and at 3, 6 and 12 months post-operative with a correction for the cyst surface (since the volume of the cyst may be responsible for more/less influence on the ovarian reserve)
- AMH modifications at 6 and 12 months follow up
- Cyst recurrence rate at 3, 6, 12 and 24 months postoperatively (visualized by transvaginal ultrasound)
- Clinical pregnancy (as defined by the ICMART (16) as a pregnancy diagnosed by ultrasonographic visualization of one or more gestational sacs or definitive clinical signs of pregnancy. It includes ectopic pregnancy. Note: Multiple gestational sacs are counted as one clinical pregnancy.)
- Ectopic pregnancy (as defined by the ICMART (16) as a pregnancy in which implantation takes place outside the uterine cavity)
- Miscarriage (defined as a spontaneous loss of pregnancy)
- Live birth (as defined by the ICMART (16) as the complete expulsion or extraction from its mother of a product of fertilization, irrespective of the duration of the pregnancy, which, after such separation, breathes or shows any other evidence of life, such as heart beat, umbilical cord pulsation, or definite movement of voluntary muscles, irrespective of whether the umbilical cord has been cut or the placenta is attached.

- Evolution of pain patterns pre- and postoperatively: each endometriosis related pain complaint will be evaluated using the NRS scale at each visit.
- POI postoperatively

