## 8. STATISTICAL ANALYSIS

### 8.1 Sample size calculation:

Sample size calculation is based on the primary outcome: evaluation of serum AMH 3 months after the specific surgical treatment.

Power calculation of this study was based on the findings of the RCT from Candiani et al (8) where AMH was a secondary outcome in comparing conventional cystectomy versus CO2 laser vaporization. In this paper a postoperative AMH of  $1,9 \pm 0,9$  ng/mL was found after CO2 laser vaporization only. In this paper a difference in decline in postoperative AMH of 50% was observed in favor of the vaporization group, although this study was not powered for this outcome. Since we will compare two conservative techniques for endometrioma surgery, a difference of 30% AMH decline after surgery was considered to be clinically relevant (after consultation of all participating centers). Based on Candiani et al. (2018) a mean serum AMH of 1.9 (SD=0.9) ng/mL is expected with CO2 laser vaporization. Assuming a common standard deviation a total sample size of 82 patients is needed (or 41 patients in each group) based on a two-sided independent t-test with alpha equal to 0.05 to have at least 80% power to detect a difference of 30% between both groups. Note that this calculation is based on the conservative assumption of no correlation between baseline AMH and AMH after 3 months.

In practice, the power is expected to exceed largely 80% since the final analysis will be based on an ANCOVA approach. However, since the study wants to gather information on multiple endpoints, we deemed it not appropriate to lower the sample size.

To account for the 10% drop out because of pregnancy within 3 months postoperatively, it is prudent to aim for a total sample size of 92 patients (or 46 patients in each group).

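### Section 8.4 divides AMH by a fixed preoperative cyst surface, which does not deliver the correction for cyst size that section 6.1.2 promises

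*Protocol*

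**What the plan says.** Sections 2 (Secondary Objectives) and 6.1.2 of the protocol list the endpoint as "AMH difference/cyst surface between baseline and at 3, 6 and 12 months post-operative with a correction for the cyst surface". The reason given is that cyst volume may change the influence on ovarian reserve.

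Section 8.4 gives the analysis in one sentence: "The ratio of the AMH and the cyst surface will be analyzed using the same methodology as used for the AMH". That methodology is the constrained longitudinal data analysis (cLDA) of section 8.3, in which "both the baseline and post-baseline values are modeled as dependent variables". Centre is the only added factor. The scale is left open: "A (logarithmic) transformation of the AMH will be considered to obtain a more symmetric distribution of the model residuals".

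"Cyst wall surface" appears in the baseline tables of sections 6.1.3 and 8.2 and not among the follow-up variables. Section 4.2 admits cysts with a mean diameter of 2.5 to 8 cm.

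**The concern.** The endpoint definition promises an AMH comparison that allows for cyst size. The analysis section divides AMH by a number that is the same for a patient at every visit. Division by a patient-level constant is not adjustment, because no relation between cyst size and AMH is estimated. What it does instead depends on the scale, which is still open.

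The two sections also name different quantities: an AMH difference over surface in 6.1.2, and AMH over surface in 8.4. As written, the analysis cannot say whether a technique effect on AMH persists once cyst size is allowed for. On the raw scale it also gives up precision.

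**Working it through.** **Inputs from the protocol.** Postoperative AMH 1.9 ng/mL, SD 0.9; difference 30%; two-sided alpha 0.05; 41 evaluable per arm (section 8.1). Diameter 2.5 to 8 cm (4.2).

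**Assumptions (not in the protocol).** Spherical cysts; the cyst-size distribution; the correlation of baseline with 3-month AMH (section 8.1 uses 0 as a conservative value); log-AMH SD 0.45; the slope of 3-month log AMH on log surface; baseline mean 2.6 ng/mL in the raw-scale runs. With two visits and complete data, the cLDA treatment effect equals ANCOVA, which was used here without centre.

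**1. The plan's own figure.** Difference 0.30 × 1.9 = 0.57. Normal approximation: n = 2 × (1.960 + 0.842)² × 0.9² / 0.57² = 39.1, so 40 per arm. The exact t-test needs 40.12, so 41 per arm, 82 in total (power 80.9%). 82 / 0.9 = 91.1, so 92. This reproduces section 8.1. The ratio endpoint has no power claim of its own.

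**2. Log scale, within patient.** log(AMH_t/S) − log(AMH_0/S) = log AMH_t − log AMH_0. Surface S cancels exactly from the change.

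**3. Log scale, in the model.** The cLDA is not a pure change score. With baseline slope b, regressing log(AMH_t/S) on log(AMH_0/S) is the same as modelling log AMH_t = a + b log AMH_0 + (1 − b) log S + arm effect. So log S stays in, with its coefficient forced to 1 − b.

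Take diameters uniform on 2.5–8 cm. Then E[ln d] = 1.60815, E[(ln d)²] = 2.69164, Var(ln d) = 0.1055 and Var(log S) = 4 × 0.1055 = 0.422. With log SD 0.45 (variance 0.2025) and correlation 0.7:

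- True slope 0: b = (0.7 × 0.2025 + 0.422) / (0.2025 + 0.422) = 0.903. Forced coefficient +0.097; correct value 0.
- True slope −0.2: b = (0.7 × 0.2025 + 1.2 × 0.422) / 0.6245 = 1.038. Forced coefficient −0.038; correct value −0.2.

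In both cases the forced value is not the one that would correct for size.

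**4. Chance imbalance in cyst size.** If one arm's cysts are 10% wider, log S differs by 2 × ln 1.1 = 0.191. The shift in the arm effect is (true slope − coefficient used) × 0.191:

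| True slope | Plain log AMH | Log ratio | Log AMH + log S covariate |
|---|---|---|---|
| −0.2 | −0.038 | −0.031 | 0 |
| 0 | 0 | −0.019 | 0 |

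Simulation agrees: −3.8% and −3.0% in the first row, about −2% for the log ratio in the second, and about 0 for the covariate model in both.

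**5. Raw scale, weights.** Surface is π × 2.5² = 19.6 cm² to π × 8² = 201 cm², a ratio of (8/2.5)² = 10.24. The same AMH fall of 0.70 ng/mL counts as 0.70/19.6 = 0.036 per cm² at one limit and 0.70/201 = 0.0035 at the other. The effective-sample fraction for weights w = 1/d² is E[w]²/E[w²]. For uniform diameters, E[w] = (1/2.5 − 1/8)/5.5 = 0.0500 and E[w²] = (1/2.5³ − 1/8³)/(3 × 5.5) = 0.00376, giving 0.665, or about 27 of 41 per arm. It is 79% for diameters normal 4.5 (SD 1.2) cm and 74% for normal 5 (SD 1.5) cm.

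**6. Power on the raw scale with the protocol's mean, SD and 0.57 difference, 41 per arm.**

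| Correlation | Uniform: AMH + S covariate / ratio | Normal 4.5 (1.2): AMH + S covariate / ratio |
|---|---|---|
| 0 | 80% / 53% | 80% / 61% |
| 0.5 | 90% / 76% | 90% / 82% |
| 0.7 | 97% / 90% | 97% / 93% |

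For uniform diameters, AMH alone gives 80%, 90% and 98%, so the covariate costs almost nothing.

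**7. Power when size matters.** Log SD 0.45, correlation 0.7, slope −0.2, uniform diameters, 41 per arm:

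| Difference | Raw ratio | Raw AMH | Log ratio | Log AMH | Log AMH + log S |
|---|---|---|---|---|---|
| 20% | 52% | 76% | 77% | 82% | 87% |
| 30% | 88% | about 99% | about 99% | >99% | >99% |

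With no technique effect and no forced imbalance, rejection rates for both ratios stay near 5%.

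**The case against.** **The ratio may be meant as AMH loss per cm² of cyst wall.** That is a legitimate quantity, and because surface is constant per patient, a raw-scale cLDA of AMH/S estimates its arm contrast. On that reading inverse-surface weighting is the definition, not a fault. But section 6.1.2 describes the quantity as "with a correction for the cyst surface (since the volume of the cyst may be responsible for more/less influence on the ovarian reserve", which is a different aim. Nor is the ratio the more powerful choice there: with a simulated surgical effect proportional to surface (uniform diameters, correlation 0.7), it had 59% power against 97% for AMH with the covariate.

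**The loss is modest at the planned effect.** This stands. At 30% and correlation 0.7 the raw ratio keeps about 88–90% power under uniform diameters. At 20%, log AMH alone already reaches 82%, so about half of the gap between the log ratio (77%) and the covariate model (87%) is gain from the covariate and not harm from dividing.

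**Stronger readings that the documents do not support.**
- A reader might infer that on the log scale the division does nothing at all. That is exact only for a change score; the cLDA keeps log S with a forced coefficient.
- A reader might infer that the ratio manufactures arm differences. Randomisation protects the comparison and type I error is near 5%. When size matters, plain log AMH shifts more than the log ratio; the division adds a shift (about −2%) only when size is irrelevant and the arms happen to differ.
- The tenfold weight compares the two eligibility limits, not typical cysts.
- The protocol does not say that larger cysts lower AMH. It allows more or less influence, so the slope of −0.2 is an assumption.

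**Conclusion.** The point holds as a mismatch between the stated purpose and the stated method of one secondary endpoint. The log-scale cancellation, the forced coefficient 1 − b and the 10.24-fold weight range follow from algebra and the eligibility limits. Surface taken as π × diameter² is the only assumption in the last of these.

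The size of the precision loss rests on the assumed cyst-size distribution, correlation, SD and slope. Across the settings shown, the raw ratio loses between 4 and 27 percentage points of power against AMH with surface as covariate at the protocol's planning inputs (97% to 93% at the least, 80% to 53% at the most). The direction could reverse only if residual AMH variability grew with surface, for which the protocol gives no basis.

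The primary analysis, the sample size and the undivided AMH analyses at 6 and 12 months are unaffected. The change should be made, but the trial's main conclusion does not depend on it.

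**What to change.** In section 8.4, replace the ratio analysis. Keep AMH as the cLDA response on the scale chosen for the primary analysis. Add preoperative cyst surface (log surface if AMH is logged) and its interaction with time as covariates. Report the adjusted arm difference at 3, 6 and 12 months.

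Reword the endpoint in sections 2 and 6.1.2 to match, so that all three places name the same quantity. If AMH loss per cm² is wanted as well, list it as a separate descriptive quantity and do not call it a correction.

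The cost is a few lines of text. Diameters and cyst wall surface are already collected at baseline, so no visit, sample or patient is added.

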##### Cyst recurrence rate

Cumulative recurrences until 24 months postoperatively will be visualised using Kaplan-Meier estimates and compared using stratified log-rank tests (stratified on centre).

